## Abstract

**Background:**

Patellar tendinopathy is a major problem for many athletes, especially those involved in jumping activities. Despite its frequency and negative impact on athletic careers, no evidence-based guidelines for management of this overuse injury exist. Since functional outcomes of conservative and surgical treatments remain suboptimal, new diagnostic and therapeutic strategies have to be developed and evaluated.

Extracorporeal shockwave therapy (ESWT) appears to be a promising treatment in patients with chronic patellar tendinopathy. ESWT is most often applied after the known conservative treatments have failed. However, its effectiveness as primary therapy has not been studied in athletes who keep playing sports despite having patellar tendon pain.

The aim of this study is to determine the effectiveness of ESWT in athletes with patellar tendinopathy who are still in training and competition.

**Methods/design:**

The TOPGAME-study (Tendinopathy of Patella Groningen Amsterdam Maastricht ESWT) is a multicentre two-armed randomised controlled trial with blinded participants and outcome assessors, in which the effectiveness of patient-guided focussed ESWT treatment (compared to placebo ESWT) on pain reduction and recovery of function in athletes with patellar tendinopathy will be investigated. Participants are volleyball, handball and basketball players with symptoms of patellar tendinopathy for a minimum of 3 to a maximum duration of 12 months who are still able to train and compete. The intervention group receives three patient-guided focussed medium-energy density ESWT treatments without local anaesthesia at a weekly interval in the first half of the competition. The control group receives placebo treatment. The follow-up measurements take place 1, 12 and 22 weeks after the final ESWT or placebo treatment, when athletes are still in competition. Primary outcome measure is the VISA-P (Victorian Institute of Sport Assessment - patella) score. Data with regard to pain during function tests (jump tests and single-leg decline squat) and ultrasound characteristics are also collected. During the follow-up period participants also register pain, symptoms, sports participation, side effects of treatment and additional medical consumption in an internet-based diary.

**Discussion:**

The TOPGAME-study is the first RCT to study the effectiveness of patient-guided ESWT in athletes with patellar tendinopathy who are still in training and competition.

**Trial registration:**

Trial registration number NTR1408.

## Background

Patellar tendinopathy ('jumper's knee') is a clinical condition of gradually progressive activity-related pain at the insertion of the patellar tendon at the apex patellae [1]. Prolonged repetitive stress of the knee-extensor apparatus can lead to this common overuse tendinopathy in athletes from different sports [2]. The overall prevalence of patellar tendinopathy among elite and non-elite athletes is high and varies between 3 and 45% [3,4]. In sports characterised by high demands on speed and power for the leg extensors, such as volleyball and basketball a prevalence of respectively 44.6% and 31.9% has been reported [4]. In sports medicine centres patellar tendinopathy is one of the leading causes for athletes to consult physicians or physical therapists. Patellar tendinopathy often contributes to the decision to quit an athletic career and also causes mild but long-lasting symptoms after an athletic career [5]. The high prevalence, impact on sports performance, and chronic nature of the condition all mean that in some jumping sports, patellar tendinopathy may cause at least as much impairment in athletic performance as acute knee injuries [4].

There is no consensus on what is the most appropriate treatment for patellar tendinopathy [6,7]. Several conservative treatment modalities (e.g. physical therapy, anti-inflammatory medication, rest, exercise) and different surgical procedures for treatment of patellar tendinopathy have been described [8,9,6,7]. Overall, they have not been proven to be highly successful in relieving symptoms to such a degree that athletes can continue to participate in their sport at their full potential [8]. New treatment modalities for patellar tendinopathy have recently been introduced, based on the finding that the pathology underlying chronic (patellar) tendinopathies is not inflammatory tendinitis but a degenerative tendinosis due to a failed healing response [10].

In the last few years, extracorporeal shockwave therapy (ESWT) has also been used for the treatment of patellar tendinopathy. It seems to be a safe and promising treatment for patellar tendinopathy [11]. In most of the research on ESWT treatment for patellar tendinopathy to date, patients have been recruited in a referral-based specialist care setting. Moreover, ESWT is often only applied when other treatments have already failed. This means that most patients included in these studies have serious, chronic problems, generally to the extent that they had to stop sports participation entirely, or at least reduce their level of sports participation significantly. One can presume that patients in this stage have a decreased healing tendency and are possibly less responsive (more resistant) to all treatment modalities. To our knowledge, the effectiveness of ESWT has not been systematically investigated in athletes who have early symptomatic patellar tendinopathy and are still actively competing.

The aim of the TOPGAME study is to determine the effectiveness of ESWT on pain, symptoms and function, in athletes with patellar tendinopathy at an early stage of the disease who are still in training and competition.

## Methods/Design

### Design

The TOPGAME study (Tendinopathy Of Patella Groningen Amsterdam Maastricht ESWT) is a multicentre randomised controlled trial with blinded participants and outcome assessors, using a two-group repeated measures design with a treatment period of 2 weeks and a 22 week follow-up. Participants are randomized into an intervention ESWT group or a placebo control group. Recruitment of participants for the TOPGAME trial takes place in May-November 2008 and data collection starts in September 2008 (first half of the competition season). The ESWT and placebo treatments start in October 2008. After three ESWT or placebo treatments, the follow-up measurements take place at 1, 12 and 22 weeks after the final treatment, when athletes are still in competition. The trial profile is shown in Figure 1.

**Figure 1 F1:**
[figure not shown]
**TOPGAME Trial profile**. The Trial profile of the TOPGAME study.

The study design, procedures and informed consent procedure were approved by the Medical Ethics Committee (Number 2008/052) of the University Medical Center Groningen (UMCG), the Netherlands. All participants have to provide written informed consent.

### Study population

Recruitment of the participants is facilitated by the Dutch Basketball Association (Nederlandse Basketbalbond, NBB), Dutch Handball Association (Nederlands Handbalverbond, NHV) and the Dutch Volleyball Association (Nederlandse Volleybalbond, NEVOBO). Through both an advertisement on their website and an e-mail sent to all their athletes (aged 18-35) and the coaches of the club teams, attention is drawn to the TOPGAME-study. Recruitment is further assisted by advertisements in local, regional and national newspapers and by advertising at tournaments and games.

All athletes are invited to fill out a questionnaire on sports participation and knee problems (including a pain map) on a specially designed website http://www.topgamestudie.nl. They are also asked for their willingness to participate in the study. After this questionnaire-based screening, participants with a high likelihood of having patellar tendinopathy are contacted by mail or phone and sent written information about the study. If they still want to participate, they receive an invitation for a consultation by one of the two sports medicine physicians of the study (FH, JZ) at a sports medicine practice in their neighbourhood. The sports medicine physicians examine all the participants and clinically establish the diagnosis of patellar tendinopathy using the criteria described below. Eligible participants are included in the study after informed consent. Thereafter, baseline measurements are carried out and athletes will be randomised to either the intervention (ESWT) group or the control (placebo) group.

### Inclusion and exclusion criteria

Male and female basketball, handball and volleyball players with the following criteria are eligible for inclusion:

1. History of knee pain in the patellar tendon or its patellar or tibial insertion (pointed out in an anatomical drawing of the knee) in connection with training and competition.

2. Symptoms for over three months in the actual season or in the second half of the previous season (January-May 2008) (to exclude acute inflammatory tendon problems and de novo partial ruptures).

3. Age 18-35 years (to reduce chances of osteochondrotic diseases like Sinding-Larsen-Johanson, Osgood-Schlatter and osteoarthrosis).

4. Palpation tenderness at the corresponding painful area.

5. VISA-P score < 80. The VISA-P (Victorian Institute of Sport Assessment - patella) score is a short questionnaire measuring the severity of patellar tendinopathy by assessing pain, function and ability to play sports [12,13].

Athletes are excluded if they suffer from acute knee or acute patellar tendon injuries, have chronic joint diseases or have signs or symptoms of other (co-)existing knee pathologies. Athletes who use drugs with a putative effect on patellar tendinopathy in the last year on daily basis (e.g. non-steroid anti-inflammatory drugs, fluorquinolones) or use anticoagulants, and athletes who had knee surgery or injection therapy with corticosteroids in the last preceding three months are also excluded. Athletes with contraindications for ESWT treatment (pregnancy, malignancy, coagulopathy) are also excluded from the study.

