#### Placebo treatment

The treatment procedure for the athletes in the control group is nearly the same. Placebo treatment will be administered using the same device. The transmission gel will be applied between the focussing pad and skin of the patient, but not between applicator and focussing pad. This is invisible for the athletes, since it is inside of the device. In this way shockwaves are not or hardly conducted. Measurements of energy density provided by the manufacturer for this placebo set-up revealed negligible or only very low energy densities of less than 0,03 mJ/mm2 (Wolf GmbH, Knittlingen, Germany). The athlete will also be told that treatment can be painful but that there is inter-individual variability in pain perception. By pressing the applicator with focussing pad to the painful spot, athletes will also experience some pain. The physical therapist will also ask after every 100 impulses if the athlete can tolerate the ESWT treatment, but energy flux density will not increase during the treatment. Athletes in the placebo group will also hear the repetitive impulses generated by the ESWT-device, yet will be unaware of the dosage administered.

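### The exclusion criteria do not bar athletes who have already had ESWT to the patellar tendon, although the sham relies on athletes not recognising it

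*Protocol article*

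**What the plan says.** The section on inclusion and exclusion criteria gives two kinds of exclusion relevant here. One is a time window for earlier procedures: "athletes who had knee surgery or injection therapy with corticosteroids in the last preceding three months are also excluded". The other is specific to the study treatment: "Athletes with contraindications for ESWT treatment (pregnancy, malignancy, coagulopathy) are also excluded from the study". Neither mentions earlier ESWT, and no other criterion does.

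The abstract describes the gap that the trial addresses: "its effectiveness as primary therapy has not been studied in athletes who keep playing sports despite having patellar tendon pain". The aim at the end of the Background is worded differently and concerns "athletes with patellar tendinopathy at an early stage of the disease who are still in training and competition".

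The sham uses the same device without gel between applicator and focussing pad, so that almost no energy passes, and the level is not raised during the session. On blinding, the placebo section says: "Athletes in the placebo group will also hear the repetitive impulses generated by the ESWT-device, yet will be unaware of the dosage administered". The Randomization section accepts that the two treatments may feel different at once, and allocates whole teams to one arm partly for that reason. The primary outcome, VISA-P, is completed by the athlete. The third part of the baseline questionnaire records previous medical treatment, but the article does not link the answer to eligibility.

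**The concern.** A sham of this kind works best when the athlete has nothing to compare it with. Someone who has had ESWT to the patellar tendon knows the sensation and may notice that a session stays mild from start to finish. With a self-reported outcome, a guess about allocation can feed directly into the score.

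Team allocation does not help. It prevents teammates in different arms from comparing notes, but an athlete with earlier ESWT makes the comparison from memory. Because teammates share an arm, one such athlete could also tell the others what the real treatment feels like.

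There is a second, smaller issue. If the earlier course had a lasting effect, it is already present at baseline or still unfolding during follow-up, in whichever arm the athlete is placed. And for that athlete ESWT is not a primary therapy.

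**Working it through.** **1. Is the athlete really eligible?** Each criterion was set against an athlete with a previous course of ESWT.

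- Site of pain, symptom duration, age, palpation tenderness and VISA-P below 80: none depends on treatment history.
- Daily drug use in the last year, anticoagulants: not ESWT.
- Surgery or corticosteroid injection in the last three months: not ESWT.
- Contraindications to ESWT: pregnancy, malignancy and coagulopathy only.

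Nothing removes this athlete. The abstract describes a maximum symptom duration of 12 months, which the eligibility list omits. Even if that limit is applied, a course of ESWT within those 12 months remains possible.

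**2. How different are the two treatments?** Energy figures come from the ESWT and placebo sections.

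- Active, start of session: 0.1 mJ/mm2. Against the sham ceiling: 0.1 / 0.03 = 3.3 times.
- Active, maximum: 0.58 mJ/mm2. Against the sham ceiling: 0.58 / 0.03 = 19 times.
- Active treatment may rise one level per 100 impulses, from level 5 to level 20: 15 steps x 100 = 1500 of the 2000 impulses. The maximum can thus be reached within one session. The sham does not rise.

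**3. Is carry-over plausible on the trial's own timeline?** Follow-up runs to 22 weeks after the last session, so the design allows for an effect at that distance. Treatment starts in October 2008, and 22 weeks before 1 October 2008 is 30 April 2008. A course of ESWT in spring 2008 would lie about that far back, and the criteria would admit the athlete.

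**4. Size, as an illustration only.** First the plan's own figure, with difference 15, SD 19, two-sided alpha 5% and power 90%:

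n per group = 2 x (1.96 + 1.2816)^2 x 19^2 / 15^2 = 33.7, so 34. With 20% drop-out, 34 / 0.8 = 42.5, so 43 per group and 86 in total. Both figures reproduce.

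Now assume that a share f of entrants shows no effect at all:

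- Diluted difference = 15 x (1 - f).
- Standard error = 19 x sqrt(2/34) = 4.61.
- Power = Phi(difference / 4.61 - 1.96).

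| f | Difference | Power at 34 per group |
|---|---|---|
| 0 | 15.0 | 90% |
| 5% | 14.25 | 87% |
| 10% | 13.5 | 83% |
| 20% | 12.0 | 74% |

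The documents give neither f nor a response rate in previously treated athletes. The table also covers one direction only. Recognition of the sham could widen the observed difference if athletes who guess their arm shift their scores accordingly. The net sign is therefore not known.

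**The case against.** **The sham has safeguards.** Athletes in both arms are told that pain perception varies, the applicator pressure causes some pain, the device can be heard, and tolerance is asked after every 100 impulses. These stand as partial protection, and the documents do not show that experience defeats them. But they work on expectation, and someone who has felt the real treatment brings a different expectation.

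**Pretreated athletes may be rare and should balance.** Recruitment is open, through sports associations and advertising, and nothing suggests that earlier ESWT is common. Randomisation should spread such athletes over both arms on average, and previous treatment is recorded. This stands against any claim of systematic confounding at baseline. It does not answer loss of blinding, which arises after allocation.

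**The article is condensed.** A fuller protocol may exclude earlier ESWT. That is possible, but the article does set out its ESWT-specific exclusions and a look-back for earlier procedures, and earlier ESWT is in neither.

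**A broader complaint is tempting but not supported.** A reader might infer that surgery or steroid injection more than three months ago should also bar entry, since the Background says of patients in earlier studies that "patients in this stage have a decreased healing tendency and are possibly less responsive (more resistant) to all treatment modalities". That sentence follows a description of patients who had stopped or much reduced sport, and the formal aim selects on early stage and continued play, not on being untreated. Likewise, the recalcitrant cases in the Discussion are athletes with several earlier conservative treatments. It does not mention earlier surgery or failed ESWT. How far back to look for surgery and injections is a choice about breadth of eligibility.

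**Conclusion.** The point holds for previous ESWT to the patellar tendon, and only for that. The criteria admit such athletes at any interval, while the trial depends on a low-energy, untitrated sham, a self-reported outcome and a gap described as primary therapy. This is a cheap improvement and not a flaw that invalidates the design.

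The size cannot be established. It depends on how many athletes have had ESWT before, whether they recognise the sham, and whether they speak to teammates. The first is not in the documents and the other two are inferences. A reader might take the drop from 15 to 13.5 points, with power of about 83%, as an estimate of harm. It is not one: the 10% share is assumed, and so is zero effect, whereas the Background says no more than "possibly less responsive (more resistant) to all treatment modalities", and says it of a different group.

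**What to change.** Add to the exclusion criteria: any previous ESWT to either patellar tendon. Apply it at screening, before inclusion, by moving forward the question on previous treatment that the baseline questionnaire already contains. The three-month limit for surgery and injections can stay as it is, and the sample size calculation does not change.

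The cost is one line of text, a few lost candidates and slightly narrower generalisability, in keeping with the stated gap. The number lost is exactly the unknown share: if it is small the loss is small, and if it were as high as 10% of 86 (about 9 athletes) the case for excluding them would be stronger.

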### Randomization

Volleyball, handball and basketball players with patellar tendinopathy are allocated randomly and blinded to an intervention group (patient-guided ESWT) or a control group (placebo treatment) by an independent statistician (EV) who is blinded for any baseline characteristics of the participants. Randomisation is performed before the first treatment by means of a computer-generated randomisation list (SPSS 16, Chicago, USA). The randomisation procedure takes place at team level, resulting in players from the same teams being allocated to the same group. While the different treatment methods within the study groups potentially have various immediately noticeable effects on the subjects (e.g. level of pain), this method of randomisation is chosen to keep the treatment group blinded to the subjects, and to avoid spill-over of the intervention. The independent physical therapists who administer the ESWT or placebo treatment are informed by the statistician about the group allocation. Group allocation is concealed from the athletes and the outcome assessor at all times during the trial.

### Intervention

ESWT treatment and placebo treatments will be given by five independent physical therapists at four different locations across the Netherlands.

#### ESWT treatment

The physical therapist will explain the treatment procedure to the athlete and will palpate the patellar tendon to find the most painful spot. ESWT is applied according to the guidelines of the International Society for Musculoskeletal Shockwave Therapy (ISMST) using a piezo-electric ESWT device (Piezowave, Wolf GmbH, Knittlingen, Germany). This will be administered in three sessions at one-week intervals using 2000 impulses at a frequency of 4 Hz. The energy flux density will be titrated according to individual pain tolerance up to a possible maximum of 0.58 mJ/mm2 (level 20). Treatment will start at level 5 (0.1 mJ/mm2). The athlete will be told that treatment can be painful but that there is inter-individual variability in pain perception. After every 100 impulses the physical therapist will ask the athlete, if he/she can tolerate the treatment. If he/she can, the physical therapist will increase the energy flux density by one level, up to the aforementioned maximum level. A transmission gel will be applied between the applicator and the focussing pad as well as between the focussing pad and the skin of the patient to optimise shockwave transmission to the patient. No local anaesthesia will be used, since Rompe and colleagues demonstrated that repetitive application of shockwaves is more effective without than with local anaesthesia [14]. The athlete will be in supine position with an extended knee and shockwaves will be focused on the painful zone in the tendon or insertion. The inferior pole of the patella will be tilted to focus on the dorsal insertion of the patellar tendon as well. The aforementioned treatment protocol was chosen based on our previous experience with ESWT application in patients with patellar tendinopathy (submitted). All patients in the pilot study tolerated this procedure well without adverse complications.

#### Placebo treatment

The treatment procedure for the athletes in the control group is nearly the same. Placebo treatment will be administered using the same device. The transmission gel will be applied between the focussing pad and skin of the patient, but not between applicator and focussing pad. This is invisible for the athletes, since it is inside of the device. In this way shockwaves are not or hardly conducted. Measurements of energy density provided by the manufacturer for this placebo set-up revealed negligible or only very low energy densities of less than 0,03 mJ/mm2 (Wolf GmbH, Knittlingen, Germany). The athlete will also be told that treatment can be painful but that there is inter-individual variability in pain perception. By pressing the applicator with focussing pad to the painful spot, athletes will also experience some pain. The physical therapist will also ask after every 100 impulses if the athlete can tolerate the ESWT treatment, but energy flux density will not increase during the treatment. Athletes in the placebo group will also hear the repetitive impulses generated by the ESWT-device, yet will be unaware of the dosage administered.

